# Study synopsis

| *Title:* | Living Well after Breast Cancer |
| --- | --- |
| *Sponsor:* | N/A |
| *Funding:* | NHMRC Project Grant APP1024739  $840,535 (2012-2015) |
| *Primary objective:* | To evaluate the telephone-delivered weight loss intervention compared to usual care, on its ability to promote and maintain weight loss, and to improve body composition, physical activity, dietary intake, clinical biomarkers of metabolic health (glucose, lipids, insulin, leptin, adiponectin, C Reactive Protein), genomic and DNA methylation-based biomarkers, blood pressure and patient-reported outcomes (quality of life, body image, fatigue, menopausal symptoms, fear of cancer recurrence). |
| *Rationale:* | Sixty percent of women with breast cancer are overweight and experience poorer outcomes (greater recurrence, reduced survival and increased risk of obesity-related chronic disease) compared to their healthy weight counterparts. Weight management support is recommended, but not integrated into clinical care. |
| *Study design:* | Randomised Controlled Trial |
| *Sample size (by treatment group):* | 80 per group (160 in total) |
| *Study arms (interventions and controls):* | Weight loss support; Usual Care |
| *Study endpoints (primary and secondary):* | Primary endpoint: 12 months (end of intervention)  Secondary endpoint: 18 months (end of study) |

# Study objectives

## Primary objective

To evaluate the telephone-delivered weight loss intervention compared to usual care, on its ability to achieve weight loss, and to improve body composition, physical activity, dietary intake, clinical biomarkers of metabolic health (glucose, lipids, insulin, leptin, adiponectin, C Reactive Protein), genomic and DNA methylation-based biomarkers, blood pressure and patient-reported outcomes (quality of life, body image, fatigue, menopausal symptoms, fear of cancer recurrence).

## Secondary objective

To assess whether changes in the primary and secondary outcomes are maintained 6-months after the end of the intervention.

To evaluate the cost effectiveness of the telephone-delivered weight loss intervention compared to usual care.

To explore mediators and moderators of the intervention effect on primary and secondary outcomes to understand how the intervention worked and for whom.

To explore whether certain genomic profiles are associated with greater weight loss success and weight loss maintenance.

# Background

## Justification/ Significance

Approximately 60% of Australian women diagnosed with breast cancer are overweight or obese [[1](#_ENREF_1)]. Excess body weight at diagnosis has been associated with an increased risk of distant recurrence and increased risk of death from breast cancer and overall mortality [[2](#_ENREF_2), [3](#_ENREF_3)]. This association has been observed in both pre- and post-menopausal women and is independent of tumour stage, adjuvant chemotherapy and endocrine treatment. Excess body weight also increases the risk of co-morbidities, such as type 2 diabetes and cardiovascular disease [[4](#_ENREF_4)]. International and Australian data show that the prevalence of co-morbidities is high among women with breast cancer (43% with at least one co-morbid condition)[[5](#_ENREF_5), [6](#_ENREF_6)] and that almost half of deaths are attributable to non-cancer causes [[7](#_ENREF_7), [8](#_ENREF_8)].

The mechanisms by which adiposity adversely affects breast cancer outcomes are unclear but likely due to a number of pathways [[9](#_ENREF_9)]. A number of metabolic biomarkers are known to be adversely affected by obesity – oestrogen, insulin, insulin-like growth factors, adipokines (e.g. leptin, adiponectin), inflammatory markers (e.g. tumour necrosis factor-alpha, interleukin-6, C-reactive protein [CRP]) [[9](#_ENREF_9)]. These biomarkers are all involved in a number of plausible biological pathways contributing to tumour-related angiogenesis and cellular proliferation [[9](#_ENREF_9)]. Recent epidemiological studies have linked a number of these metabolic biomarkers (i.e. insulin, leptin, adiponectin, CRP) to breast cancer recurrence, diseases-specific mortality and overall survival [[7](#_ENREF_7), [10-13](#_ENREF_10)]. Novel genomic markers may also play an important role in the association between excess body weight and poorer breast cancer outcomes [[14](#_ENREF_14)].

Only four randomised controlled trials have evaluated weight loss interventions for women with breast cancer [[15-18](#_ENREF_15)]. These trials evaluated shorter-term interventions with only one trial examining a 12 month intervention [[16](#_ENREF_16)]; none evaluated whether this weight loss was maintained following intervention completion; most recruit women a number of years after their diagnosis; and none have been conducted in Australia. Only two of these trials reported on changes in blood lipids (triglycerides, HDL-cholesterol), and one assessed changes in insulin and leptin (although these outcomes were underpowered) [[16](#_ENREF_16), [17](#_ENREF_17)]. Thus there is currently limited evidence on the effectiveness of weight loss interventions to achieve successful weight loss maintenance and to improve a range of metabolic and cancer-related biomarkers.

Two large-scale dietary-change (low fat and high fruit/vegetables, but not weight loss) intervention trials in women with breast cancer have followed women for 5-7 years to evaluate the impact on disease-free survival [[19](#_ENREF_19), [20](#_ENREF_20)]. One of these trials observed a beneficial impact on breast cancer recurrence (in concert with 3% weight loss) [[19](#_ENREF_19)]. Evidence from physical activity-only intervention trials demonstrates significant improvements in quality of life and treatment side-effects [[21-23](#_ENREF_21)]; along with some evidence for improvements in serum insulin and inflammatory marker concentrations [[24](#_ENREF_24)]. Evidence from observational studies suggests that post-diagnosis physical activity reduces risk of breast cancer recurrence, breast cancer mortality and overall mortality [[25](#_ENREF_25)]. The evidence suggests that improvements in physical activity and diet are likely to have independent beneficial impacts on a range of outcomes relevant to improving both the quantity and quality of survival in women with breast cancer.

The major Australian and North American cancer organisations now recommend that weight management should be a part of standard care for overweight women diagnosed with breast cancer [[26-29](#_ENREF_26)]. However, currently in Australia very little is done to provide weight management services as part of follow-up care; our own work shows that less than 25% of overweight and obese breast cancer survivors report receiving advice regarding weight management. Findings from this trial will inform the care of Australian women with breast cancer.

This study will evaluate the effectiveness of a weight loss intervention, compared to usual care, for women following treatment from breast cancer on a range of outcomes including weight and body composition, metabolic and genomic biomarkers and patient-reported outcomes. The intervention is delivered via the telephone to improve access to the intervention and allow for longer-term repeated contacts between the Coach and participant to improve the likelihood of successful weight loss maintenance. A cost-effectiveness analysis will inform decisions regarding the future delivery of the program.

# Study design

## Research question(s)/ aim(s)

The aims of the study are to:

1. To evaluate the telephone-delivered weight loss intervention compared to usual care, on its ability to promote and maintain weight loss, and to improve body composition, physical activity, dietary intake, clinical biomarkers of metabolic health (glucose, lipids, HbA1c, insulin, leptin, adiponectin, C Reactive Protein), genomic and DNA methylation-based biomarkers, blood pressure and patient-reported outcomes (quality of life, body image, fatigue, menopausal symptoms, fear of cancer recurrence).
2. To evaluate the cost effectiveness of the telephone-delivered weight loss intervention compared to usual care.
3. To explore mediators and moderators of the intervention effect on primary and secondary outcomes to understand how the intervention worked and for whom.
4. To explore whether certain genomic profiles are associated with greater weight loss success and weight loss maintenance.

## Hypotheses

1. Weight loss from baseline to 12-months follow-up, expressed as percent of initial body weight, will be at least 5% greater in the intervention group compared to the usual care group.

1b. Participants in the intervention group will report significantly greater improvements in all secondary outcomes (body composition, physical activity, diet, metabolic and genomic biomarkers, blood pressure, and patient reported outcomes) compared to the usual care group at the end of intervention (12-months).

1c. Differences observed between intervention and usual care groups for primary and secondary outcomes at 12-months will be maintained at 18-months follow-up.

2. The intervention will be cost-effective (less than $50,000 per disability-adjusted life year), compared to usual care.

Aims 3 and 4 are exploratory and not hypothesis testing.

## Study design

**Design:** This is a randomized controlled trial, with participants randomly allocated to one of two groups: 12-month weight loss support intervention or usual care.

**Data Collection:** Data collection points occur at baseline, 6-months (short-term), 12-months (end-of-intervention) and 18-months (maintenance post-intervention).

See Figure 1 for an overview of the study design

**Baseline 6 months 12 months 18 months**

Intervention Intensive phase: Maintenance Phase: Study newsletter Study newsletter

6 x weekly calls; 6 x monthly calls plus SMS (no telephone contact) (End of study)

10 x fortnightly calls

Usual Care Study newsletter & Study newsletter & Study newsletter & Study newsletter

brochures brochures brochures (End of study)

**Data**

**Collection X X X X**

**Figure 1:** Living Well after Breast Cancer study design

# Study population

The study population is women diagnosed with breast cancer who have recently completed treatment and are overweight or obese at the time of study enrolment. Potential participants will be identified through six Brisbane hospital sites (Royal Brisbane and Women’s Hospital, Redcliffe Hospital, Mater Public Hospital, Mater Private Hospital, Greenslopes Private Hospital, North West Private Hospital and Holy Spirit Northside Private Hospital) between October 2012 and February 2014. In addition, patients diagnosed with breast cancer from 1 July 2013 to 30 June 2014 will be identified through the Queensland Cancer Registry (via electronic pathology reports), or until the target sample size for recruitment has been achieved.

## Inclusion criteria

Eligibility will be based on the following inclusion criteria:

- Women
- Stage I-III breast cancer
- Aged 18-75 years
- BMI 25-45 kg/m^2^
- Finished primary treatment (i.e., surgery, chemotherapy and/or radiotherapy)

## Exclusion criteria

Women will be excluded if they meet any of the following criteria:

- Ductal carcinoma in situ (DCIS; stage 0) or distant metastases (stage IV)
- Diagnosed more than two years ago
- Pregnant
- Contraindications to participating in an unsupervised program (active heart disease, impaired mobility)
- Taking warfarin
- Greater than 5% weight loss in previous 6 months
- Insufficient English to complete assessments and participate in telephone-delivered program
- Unable to travel to Brisbane to complete study assessments
- Reporting depression/anxiety as a current significant problem that would interfere with study participation

## Withdrawal criteria

Participants will be withdrawn from the study if they report any of the following during the course of the study:

- Cancer recurrence or new cancer diagnosis
- Contraindications to participating in unsupervised physical activity, dietary or weight loss program (mobility issues, recent heart attack or angina, breathing difficulties requiring hospitalization or oxygen use, use of warfarin, pregnancy) – *Note: if a participant becomes pregnant during the course of the study, they may continue to receive intervention calls if they wish, with their doctor's approval*
- Moving interstate/overseas and therefore unable to complete study assessments

Participants are free to withdraw from the study at any point. If an intervention participant indicates that they wish to withdraw from the study they will be given the opportunity to withdraw from the intervention (and not receive any further telephone calls) but continue to complete the study assessments or to withdraw from the study completely and no complete any further intervention calls or study assessments.

Participants who choose to withdraw completely from the study will be asked to provide a reason for withdrawing which will be documented in the study database. Following this, participants will receive no further contact in relation to the study. Data collected from participants up until the point of withdrawal will be kept in the study database and used in data analysis. The study target sample size of 160 participants allows for attrition and therefore additional participants will not be recruited to replace withdrawing participants.

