### 5.3.1 Intervention group

The weight loss intervention will use a combined approach of increasing physical activity, reducing energy intake and behaviour change strategies. The intervention will be delivered entirely over the telephone by lifestyle coaches (who will be Accredited Practising Dietitians with additional study-specific training in exercise promotion). The intervention will be delivered over 12 months, with an initial intensive 6-month phase involving 16 calls (6 x weekly calls, 10 x fortnightly calls) followed by a 6-month maintenance-enhancement phase involving 6 monthly calls. Telephone calls will be scheduled based on participant preference (day vs. night). Participants will also receive a detailed workbook, set of digital scales, measuring tape, pedometer, kilojoule/calorie counter book and self-monitoring diary, which will be referred to over the 12-month intervention. Intervention participants will also be posted the same brochures and newsletter that the usual care participants receive (see below).

Participants will be encouraged to aim for weight loss of between 5-10% of their starting body weight. The physical activity component of the intervention includes both aerobic and resistance exercises, consistent with physical activity guidelines for cancer survivors. Women will be encouraged to slowly work towards a target of 30 minutes of moderate-level activity per day (210 minutes per week) and 2-3 sessions of resistance exercise per week. For diet, participants will be encouraged to reduce energy intake by 2000kJ. Participants will be prescribed a recommended kilojoule intake (between 5,000 – 7,500 kJ/day) based on age and baseline weight. Coaches will provide individualised advice including improving portion control, reducing energy density and eating regular meals along with kilojoule counting to achieve this energy reduction. In addition, participants will be encouraged to aim for total fat intake < 30% of energy, saturated fat intake < 7% of energy, 5 serves per day of vegetables and 2 serves per day of fruit. Both coach and participant will be provided with detailed feedback on the participant’s baseline and follow-up assessments (body composition, dietary intake, physical activity, blood test results) to monitor progress.

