## Assessment schedule and follow up

Study assessments will be conducted at baseline, 6-months, 12-months and 18-months. Each study assessment will involve participants:

1. attending the body composition laboratory for an assessment;
2. attending a local pathology collection centre for a blood test;
3. wearing two activity monitors over seven (7) days (and returning monitors via post);
4. completing two telephone interviews;
5. completing a questionnaire.

| **Time point:** | **Hospital recruitment** | **Screening/ recruitment** | **Baseline assessment**  **(BL)** | **6-month assessment**  **(6M)** | **12-month assessment**  **(12M)** | **18-month assessment**  **(18M)** | **Early Termination** |
| --- | --- | --- | --- | --- | --- | --- | --- |
| **Inclusion criteria** | x |  |  |  |  |  |  |
| **Consent to contact** | x |  |  |  |  |  |  |
| **Informed consent** |  | x |  |  |  |  |  |
| **Exclusion Criteria** |  | x |  |  |  |  |  |
| **Case report forms** |  | x |  |  |  |  | x |
| **Randomisation/allocation** |  |  | x |  |  |  |  |
| **Body composition assessment** |  |  | x | x | x | x |  |
| **Blood sample collection** |  |  | x | x | x | x |  |
| **Activity monitor wear** |  |  | x | x | x | x |  |
| **Telephone interview** |  |  | x | x | x | x |  |
| **Questionnaire** |  |  | x | x | x | x |  |
| **Adverse events** |  |  |  | x | x | x |  |
| **Participant satisfaction (Intervention only)** |  |  |  |  | x |  |  |

At baseline, participants must complete the body composition assessment, have a blood sample taken, complete the physical activity measurement (wearing the hip and thigh monitors) and telephone interviews in order to be randomised into the study. Whilst it is desirable for participants to also complete the self-report questionnaire, and this will be encouraged, this data is not essential and participants can be randomised even if this is incomplete. Participants who fail to complete all the essential assessment components will not be randomised into the study.

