### 5.6.1 Body Composition Assessment

The first component of each assessment to be completed is the Body Composition Assessment. The Body Composition Assessment is to be completed at the Body Composition Laboratory at the Royal Children’s Hospital. A laboratory technician, with the appropriate accreditation will conduct the assessment (appendix g).

The following data will be collected:

- Self-reported pre-diagnosis weight
- Height (stadiometer)
- Weight (digital scales)
- Waist circumference (non-expandable tape at top of iliac crest)
- Hip circumference (non-expandable tape at widest point of the buttocks)
- Blood pressure (Omron T8)
- Whole-body and segmental body composition - fat mass, fat-free mass (Lunar Prodigy DEXA scanner)
- Bone mineral density – hip and lumbar spine (Lunar Prodigy DEXA scanner)
- Physical functioning – hand grip strength (Smedley handheld dynamometer); timed chair stands (5 sit-to-stand repetitions)

At this assessment, participants will be provided with the pathology request form for the blood sample collection and two 5ml SST tubes to take with them to the Sullivan Nicholaides Pathology (SNP) Collection Centre, the activity monitor pack (including the hip and thigh monitors and express postage return pack), a food model booklet for use in the telephone interviews and the self-report questionnaire (with reply-paid envelope).

Body composition and bone mineral density will be measured by a DEXA machine. Having a DEXA scan done is similar to having an x-ray but has about 10% of the radiation of a chest x-ray.

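### The relocation rule takes women who move away out of the whole study, although only the laboratory visit ties follow-up to Brisbane

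*Protocol*

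**What the plan says.** Section 4.3 (Withdrawal criteria) opens with "Participants will be withdrawn from the study if they report any of the following during the course of the study", and its third bullet is "Moving interstate/overseas and therefore unable to complete study assessments". The withdrawal is from the study, not only from the intervention. In the schedule table of section 5.6, the early-termination column marks case report forms and no outcome assessment.

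The same section offers a middle course, but only to intervention participants who say they want to withdraw. They may "withdraw from the intervention (and not receive any further telephone calls) but continue to complete the study assessments". Nothing comparable is written for movers, or for anyone in usual care.

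At entry, section 4.2 excludes women who are "Unable to travel to Brisbane to complete study assessments". On delivery, section 5.3.1 says "The intervention will be delivered entirely over the telephone by lifestyle coaches".

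Section 5.6 lists five assessment components. One is "attending the body composition laboratory for an assessment", and section 5.6.1 fixes its place: "The Body Composition Assessment is to be completed at the Body Composition Laboratory at the Royal Children’s Hospital". The others are blood at a local collection centre, activity monitors sent back by post, two telephone interviews, and a questionnaire that section 5.6.5 offers on paper or electronically.

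**The concern.** The bullet presents inability to complete assessments as following from the move. For at least two of the five components that does not follow. A woman who can no longer reach the laboratory can still answer the telephone and fill in an online questionnaire, yet the rule ends these along with the laboratory visit.

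What is at stake is outcome data after randomisation, lost for a reason unrelated to health or willingness. The outcomes collected remotely include physical activity, energy intake, quality of life and body image, for which section 8.1.2 claims at least 80% power. They also include fatigue, menopausal symptoms and fear of recurrence, which fall in the group with only 50% to 80% power. Hypothesis 1b covers all of them. Section 4.3 says withdrawn women are not replaced.

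**Working it through.** **Step 1. What each component needs (sections 5.6 to 5.6.5).**

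| Component | Link to the laboratory as written | After a move |
| --- | --- | --- |
| Body composition | Done at one named laboratory; yields weight, DEXA, girths, blood pressure, physical function | Only if she can travel back |
| Blood | Local centre of one named provider; form and tubes given out at the laboratory; samples couriered within Brisbane | No interstate or overseas arrangement stated; not counted as recoverable |
| Activity monitors | Returned by post, but the pack is given out at the laboratory | Possible if posted out |
| Two telephone interviews | None for the call; the food model booklet is given out at the laboratory | Possible; booklet to be posted |
| Questionnaire | Paper copy given out at the laboratory; electronic version exists | Possible |

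One component needs the laboratory, two can be done remotely, one can be if the pack is posted, and one cannot be settled from the protocol (1 + 2 + 1 + 1 = 5).

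**Step 2. How the bullet can be read.**

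- Reading A: the move itself triggers withdrawal, and inability is presumed.
- Reading B: withdrawal applies only if the move prevents some part of the assessment.
- Reading C: withdrawal applies only if it prevents every part. The rule would then hardly ever apply, since interviews are by telephone.

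Under A and B, a woman who can do the interviews and questionnaire but not the laboratory visit leaves the study. The text does not say which reading is meant.

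**Step 3. The stated sample size (section 8.1.1).** Inputs: difference 5, SD 8.5, two-sided alpha 5%, power 90%, attrition 25% at 18 months.

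- Evaluable per group: n = 2 × (1.960 + 1.282)² × 8.5² / 5² = 60.7, so 61.
- Inflated: 61 / 0.75 = 81.3, so 82 per group, against 80 stated.
- In reverse: 80 × 0.75 = 60 per group gives power 0.897 (normal approximation) or 0.892 (t-test).

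The stated 80 per group is reproduced closely enough and is not in question.

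**Step 4. Size, under an assumed mover rate.** The protocol gives none. Take 2-5% over the study.

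- Movers: 0.02 × 160 = 3.2 to 0.05 × 160 = 8, so about 3-8 women.
- Attrition allowance: 0.25 × 160 = 40 women. Movers would be 3.2/40 = 8% to 8/40 = 20% of it.

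Primary power by total loss of weight data (normal approximation):

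| Loss | Per group | Power |
| --- | --- | --- |
| 20% | 64 | 0.914 |
| 22.5% | 62 | 0.906 |
| 25% | 60 | 0.897 |
| 27.5% | 58 | 0.886 |
| 30% | 56 | 0.876 |

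Each 2.5 points of loss costs about 1 point of power. Remote follow-up alone moves none of these figures, because weight is measured at the laboratory. Even if movers were 5% of the sample, fell within the 25%, and all came back to be weighed, power would rise only from 0.897 to 0.914.

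For remotely collected outcomes, expected completers are 160 - 40 = 120. Keeping 3-8 movers would add at most 3.2/120 = 2.7% to 8/120 = 6.7%.

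**The case against.** The strongest reply is that the bullet is conditional. It speaks of women who are unable to complete assessments because of the move, which parallels the entry exclusion for women who cannot travel to Brisbane. A reader might infer that a woman who moves just over the state border and can still attend must be withdrawn, or that sections 4.2 and 4.3 conflict. The wording does not firmly support either inference, because a woman who can attend is not unable. This part of the reply stands. What remains is that inability is undefined, and that missing the laboratory visit alone may take her out of everything.

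Second, remote follow-up is less complete than it looks. A reader might count interviews, questionnaire and monitors as unaffected by a move because the monitors come back by post. Section 5.6.1, however, hands out the monitor pack and food booklet at the laboratory visit, so outward posting would be a new step. Blood depends on one provider. This stands too, and is why only two components are counted as remote under present arrangements.

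Third, the laboratory visit carries the primary outcome, so a reader who infers avoidable loss of the primary endpoint goes too far. Weight is saved only for women who can return. Replacing it with local weights would trade measurement at one laboratory, by an accredited technician with blinded data collection (sections 5.4 and 5.6.1), for an uncontrolled scale. A sponsor may reasonably decline that in the primary analysis.

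Fourth, data up to withdrawal are kept, attrition is allowed for, and section 8.5 examines missing data by group and reason. These soften the loss but do not justify ending collection of outcomes that remain obtainable.

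**Conclusion.** The point holds as a modest, avoidable missing-data weakness, mainly in secondary outcomes. It is neither a calculation error nor a firm contradiction. Unless the bullet is given its most lenient reading, it removes from the whole study women who could still provide interview, questionnaire and, with posting, monitor data. The partial participation that section 4.3 allows is not open to them.

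The size cannot be determined from the protocol. At an assumed 2-5% it is about 3-8 of 160 women, well inside the 40-woman allowance, with at most about 2 points of effect on primary power. A reader might also infer that movers generally lose their treatment. That could apply only to intervention participants who move during the 12 months of calls.

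The case for change rests on low cost and on keeping randomised women in follow-up, not on a threat to the primary result.

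**What to change.** Reword the third bullet of section 4.3 so that moving is not in itself a reason for withdrawal from the study. For example: *Participants in either group who move away remain in outcome follow-up in their allocated group. They complete the telephone interviews, the questionnaire and posted activity monitors where possible, and attend the laboratory when able to travel. Only components that cannot be completed are recorded as missing, with the reason.*

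Add to section 5.6.1 that the monitor pack and food model booklet may be posted to women who cannot attend. If a weight measured elsewhere is collected, record its source and use it only in a sensitivity analysis.

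Whether intervention calls continue after a move should be stated by the sponsor, reconciling section 4.3 with telephone-only delivery in section 5.3.1. No rule on that is proposed here.

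The cost is a protocol amendment, postage and a field for weight source if local weights are taken. The downside is a few partly complete assessments.

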### 5.3.2 Usual Care group

Participants in the usual care group will continue to receive their standard medical care. In addition, these participants will be posted written materials after each of their study assessments (baseline, 6-months, 12-months, 18-months). These written materials will include brief feedback from their study assessment, off-the-shelf brochures and a study newsletter.

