# Outcomes/ Measures

## Primary outcome

- Weight loss (% initial body weight)

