# Statistical methods

## Sample size and justification

### Power for primary endpoints

The sample size calculation is based on observing an average weight loss in the intervention group at the end of the intervention (12-months) of 7% of initial body weight[[30](#_ENREF_30)] and allowing for a small regain in weight in the intervention group from 12- to 18-months (+1.2%)[[31](#_ENREF_31)] and small changes in weight among the control group (approx ±1%).[[15-18](#_ENREF_15)] Thus, we expect that weight loss from baseline to 18-months follow-up, expressed as percent of initial body weight, will be at least 5% greater in the intervention group compared to the usual care group**.** Assuming a standard deviation of change of 8.5%[[16](#_ENREF_16)] and allowing 25% attrition at 18-months,[[32](#_ENREF_32)] 80 women per group (160 participants in total) will be needed to detect this minimum difference in weight loss between groups with 90% power and a type I error of 5% (two-tailed).

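### Only intervention women who ask to withdraw are offered continued assessments, and neither arm is offered a reduced follow-up, so primary weights may be lost avoidably and unequally

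*Protocol*

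**What the plan says.** Section 4.3 (Withdrawal criteria) gives every woman the same basic right: "Participants are free to withdraw from the study at any point". The next sentence adds a retention step and names the arm: "If an intervention participant indicates that they wish to withdraw from the study they will be given the opportunity to withdraw from the intervention". She may stop the calls "but continue to complete the study assessments or to withdraw from the study completely". No parallel sentence covers a usual-care woman who makes the same request.

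For women in either arm who leave completely, a reason is requested and recorded, and then: "Following this, participants will receive no further contact in relation to the study". Data collected up to that point are kept and analysed. Women who withdraw are not replaced.

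Section 5.3.2 shows that usual care has no programme to stop. It is standard medical care plus feedback, brochures and a newsletter posted after each assessment. Section 5.6 lists five components of each assessment: the laboratory visit, a blood test, two activity monitors worn for seven days, two telephone interviews and a questionnaire. The primary outcome (Section 7.1), percent weight loss, needs only the weight from the laboratory visit (Section 5.6.1). In the schedule table the early-termination column marks case report forms but no body composition assessment, so no exit weight is planned.

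**The concern.** A randomised comparison is protected best when the effort to keep women under observation is the same in both arms. Here the instruction to staff is explicit for one arm and silent for the other. A usual-care woman who is tired of the study is tired of the assessments, since they are nearly all the study asks of her. The step that could still save her primary outcome, a shorter visit for weight alone, is not written down. Nor is it written for an intervention woman who wants to stop both the calls and the full assessments.

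Two things are at stake. First, weights that some women would have been willing to give are lost in both arms. Second, if the share or kind of women lost differs by arm, the comparison of observed weights can be biased. Section 5.4 leaves the project manager and the participants aware of allocation, so an arm-specific offer can affect retention by arm.

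**Working it through.** **Inputs from the documents (Section 8.1.1).** Difference 5 percentage points, SD of change 8.5, 80 women per group, 25% attrition at 18 months (one figure, not split by arm), 90% power, two-sided 5% level.

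**The plan's own figure.** n = 2 × (1.960 + 1.282)² × 8.5² / 5² gives 61 evaluable per arm. 61 / 0.75 rounds up to 82, close to the stated 80. Conversely, 80 × 0.75 = 60 evaluable per arm gives power 0.897. The sample size reproduces within rounding and is not in question.

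**Does unequal loss cost power?** The splits are assumptions that hold overall loss at 25% (intervention / usual care):
- 20% / 30%: 64 v 56 women, power 0.895
- 15% / 35%: 68 v 52 women, power 0.891
- 10% / 40%: 72 v 48 women, power 0.884

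Imbalance alone costs about one point of power. The issue is bias.

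**Illustration of bias in a completers' comparison.** Assumptions not in the documents: 20 of 80 women in each arm ask to leave; 10 of the 20 intervention women accept the offer and stay for assessments; all 20 usual-care women go; women who ask to leave end x points worse than those who do not.
- Usual care: the full-group mean includes a shift of 20/80 = 0.25x and the observed mean includes none, so it is too favourable by 0.25x.
- Intervention: the full-group shift is 0.25x and the observed shift is 10/70 = 0.143x, so the mean is too favourable by 0.25x − 0.143x = 0.107x.
- Contrast: 0.25x − 0.107x = 0.143x, with usual care flattered more. The effect is **understated** by 0.29 points at x = 2 and by 0.57 at x = 4.

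**A second parametrisation.** If women lost differ from those retained by g points, equally in both arms, the shift in the completers' difference is (loss in usual care − loss in intervention) × g. For g = 1 to 4 this gives 0.1 to 0.4 points at 20% / 30% and 0.2 to 0.8 points at 15% / 35%.

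**Sensitivity to the direction of imbalance.** With equal loss the shift is zero. At 30% / 20% it is (0.20 − 0.30) × g = −0.1g, so with women lost doing worse the effect is overstated.

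**Scale.** With 70 v 60 women observed, the standard error of the difference is 8.5 × √(1/70 + 1/60) = 1.5 points. The illustrative shifts of 0.29 to 0.57 are about a fifth to two fifths of it.

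**The case against.** The strongest reply is that the asymmetry largely follows from the design. The offer separates calls from assessments, and only the intervention arm has calls: 16 in the first six months and 6 in the next (Section 5.3.1). That arm carries an extra reason to leave, and the offer addresses it. If the calls prompted 10 extra intervention requests and those 10 women stayed for assessments, loss would be 20 v 20. With the women lost alike in kind, the bias would be zero. This stands, and it is why the direction cannot be stated.

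A reader might infer that usual-care women face all-or-nothing withdrawal. The text does not say so. It is silent on them, and the no-contact rule applies only to women who choose to leave completely. Section 5.6 makes components compulsory only at baseline, for randomisation. Nothing bars taking a weight alone at 12 months.

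A reader might also take 0.29 to 0.57 points as the expected bias of the trial. That is not supported. The 25% is an 18-month figure, and it does not separate voluntary requests from withdrawals that Section 4.3 itself requires, such as cancer recurrence or moving away. The acceptance rate and x are assumed. The formula compares raw completers' means, whereas Section 8.3.1 plans a linear mixed model adjusted for baseline weight, in which a woman who leaves after six months still contributes. Section 8.5 examines drop-out by group and reason, and Section 8.3.3 plans sensitivity analyses.

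These provisions do not dispose of the point. A woman who leaves before six months has no post-baseline weight for the model. Observed data cannot settle whether loss depends on the unseen weights, and Section 8.5 names a completers' analysis among its options. No analysis recovers a weight that was not taken.

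**Conclusion.** The point holds as a gap in the retention procedure. A step short of complete withdrawal is written for the intervention arm only, and a reduced follow-up for neither. Loss of the 12-month weight can therefore be avoidable in both arms and can differ between them. The documents do not show that it will differ, by how much or in which direction, so a claim that the primary result is biased would go too far.

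The figure of about 0.14x is an illustration that rests on equal numbers of requests, half of the intervention women accepting, and a completers' comparison. In that scenario the effect is understated. No sample-size figure changes. This is a cheap improvement and not a flaw that undermines the design.

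**What to change.** Reword Section 4.3 so that a woman in either arm who asks to withdraw is invited, before complete withdrawal is recorded, to continue the assessments or, as a minimum, to give the 12-month weight and, if willing, the 18-month weight. Keep the option to stop the calls for the intervention arm. Let the no-contact rule apply only after this invitation is declined. The right to withdraw at any time is unchanged.

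The cost is a few sentences of protocol text, and the weight is already a scheduled measurement. The downside is that some women may give a weight without secondary outcomes.
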